### Recruitment {15}

We will utilize the nutrition clinic to connect with potential participants and encourage their involvement. Before enrolling, we will screen for inclusion and exclusion criteria to minimize dropouts and ensure participants meet the study’s requirements. We will also offer flexible visit scheduling to accommodate participants’ schedules, increasing the likelihood of enrollment. Monthly, we will conduct a recruitment audit to monitor progress. If necessary, we will recruit participants from the university, comprehensive health care centers, and hospitals affiliated with Mashhad University of Medical Sciences to reach the target sample size.

## Assignment of interventions: allocation

### Sequence generation {16a}

Twelve blocks (each with a block size of 6) will be used to perform permuted block randomization for random allocation. Given the sample size of 72 subjects, the Random Allocation software will produce 12 blocks to form a set of sequentially numbered envelopes, each containing an equal number of assignments for either the placebo or intervention group. The study methodologist manages the study's randomization.

### Concealment mechanism {16b}

The pharmacist in charge of the study at Parsi Lact Company (Shiraz, Iran) manages the distribution of blinded placebos and supplements, which are labeled as A or B, identical in packaging, color, and taste. Allocation concealment will be carried out using sealed envelopes in the same order they were generated by the methodologist, who will be blinded to recruitment. The envelopes will be numbered and organized sequentially. For each patient enrolled in the study, an envelope following the generated sequence will be opened, and the patient will be assigned to either the control or the intervention group based on the envelope’s contents. Patient allocation and concealment will be performed by an individual not involved in the study.

### Implementation {16c}

Our study’s allocation sequence will be produced by the study methodologist using random allocation software to ensure participants are assigned fairly and randomly. The lead researcher will enroll participants after confirming their eligibility and obtaining informed consent. Once enrolled, someone not involved in the study will assign individuals to interventions, maintaining the integrity of the randomization process throughout the trial.

## Assignment of interventions: blinding

### Who will be blinded {17a}

After the interventions are assigned, participants, investigators, outcome assessors, and data analysts will remain blind to the allocations.

### Procedure for unblinding if needed {17b}

Unblinding will occur if a participant experiences a severe adverse event (SAE). To determine a participant’s assigned intervention, the designated team member will securely access the allocation code. This process will be documented to ensure transparency and accountability. After unblinding, the participant will receive appropriate medical care, and the incident will be reported to the relevant oversight bodies as required by regulations.

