### Intervention description {11a}

A hypocaloric diet (500 kcal deficit) consisting of 50% carbohydrates, 20% protein, and 30% fat will be prescribed for participants in both groups. Total energy expenditure will be calculated based on the Mifflin equation. Participants will be encouraged to engage in 150 min of physical activity per week.

This study will utilize a supplement consisting of pasteurized *Akkermansia muciniphila*, green tea extract, and glucomannan konjac, offered in 2-g sachets. The placebo is formulated with microcrystalline cellulose and also comes in 2-g sachets. Participants will be instructed to consume one sachet 30 min before every meal (breakfast, lunch, and dinner) for 8 weeks. Parsi Lact Company (Shiraz, Iran) prepared and packaged the supplements and placebos in sachet form. Both the placebo and the supplement exhibit the highest level of similarity, and the containers will remain unlabeled and coded as A or B to ensure both researchers and participants are unaware of the type of intervention they will receive. Each participant will receive a monthly supply of the sachets they need for consumption over the course of a month. To promote sachet consumption, participants will receive weekly calls and briefing messages. Compliance will be tracked by counting the monthly returned used and unused sachets. Additionally, we will assess sachet consumption through food recalls. At the beginning of the study, all participants will complete a checklist to collect their general characteristics, medical history, and information regarding medications and supplements they are currently using.

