### Criteria for discontinuing or modifying allocated interventions {11b}

For safety concerns, if a participant experiences severe or ongoing adverse effects (like unmanageable stomach symptoms or allergic reactions) due to the supplement, intervention will be stopped after discussing with a physician. The criteria for stopping or changing the assigned interventions include: (1) Safety concerns, such as severe adverse events (like anaphylaxis or severe gastrointestinal symptoms) or persistent intolerable reactions. (2) If a participant requests to stop at any time, their request will be *honored without consequence. (3) If a participant’s** condition worsens, requiring the intervention to be terminated.*

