### Adverse event reporting and harms {22}

Participants will stay in contact with the researchers once a week, and any issues or adverse effects that arise during the intervention will be discussed. If any adverse side effects or problems are identified, participants will be removed from the study after consulting with the research team and specialists in the relevant field. We follow institutional guidelines for reporting and managing adverse effects.

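### The code is broken automatically for any severe adverse event, with no test that the allocation is needed for the participant's care

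*Protocol article*

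**What the plan says.** All references are to the protocol article.

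- **Unblinding {17b}.** The trigger is unconditional: "Unblinding will occur if a participant experiences a severe adverse event (SAE"). Then "the designated team member will securely access the allocation code", the step is documented, and medical care and regulatory reporting follow. The section does not say who may be told the result.
- **Discontinuation {11b}.** Safety reasons for stopping or changing the intervention are described as "such as severe adverse events (like anaphylaxis or severe gastrointestinal symptoms) or persistent intolerable reactions". For severe or continuing adverse effects, "intervention will be stopped after discussing with a physician".
- **Product coding {11a} and {16b}.** Under the intervention description, "the containers will remain unlabeled and coded as A or B to ensure both researchers and participants are unaware of the type of intervention". Under the concealment mechanism, the company pharmacist "manages the distribution of blinded placebos and supplements, which are labeled as A or B, identical in packaging, color, and taste". Neither section mentions a participant-specific or kit-specific code.
- **Handling of sachets {11a}.** "Compliance will be tracked by counting the monthly returned used and unused sachets".
- **Harms {22}.** "If any adverse side effects or problems are identified, participants will be removed from the study after consulting with the research team" and relevant specialists.
- **Blinding {17a}.** Participants, investigators, assessors and analysts are all meant to stay blind after assignment.

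**The concern.** A code break is justified when the treating physician would act differently on knowing the allocation. Section {17b} replaces that judgement with an event type. It also pairs severe, which grades intensity, with SAE, the usual abbreviation for serious adverse event. Because {11b} gives severe gastrointestinal symptoms as an example of a severe adverse event, a tolerability problem can meet the trigger as written. The natural response to such a problem is to stop the sachets, and that is the same whether they were active or placebo.

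The person whose code is broken is a small part of the issue, since that person's sachets are stopped under {11b} and {22} provides for removal. What is at stake is the blind of the others. With two product letters, the allocation of one participant together with that participant's letter gives the meaning of both letters. The outcomes most open to such knowledge are tape-measured waist and hip circumference, which are primary, and self-rated appetite, which is secondary. Weight and fat mass are read from instruments.

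**Working it through.** The plan states no figure on this point, so there is none to reproduce. The check sets the sections side by side and then bounds the exposure.

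**Step 1. Is the break conditional on clinical need?** No. The words *if needed* stand only in the heading of {17b}. The text under it makes the event sufficient. Naming one person to open the code, and documenting the step, controls how the code is opened but not whether it should be. The discussion with a physician in {11b} governs stopping the intervention, not breaking the code.

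**Step 2. Can the trigger be met when the code is not needed?** Yes, as written. {17b} and {11b} use the same term, severe adverse event, and {11b} includes severe gastrointestinal symptoms. {11b} also supplies a response, stopping the sachets, that can be carried out blind. A break in that situation adds nothing to the decision to stop.

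**Step 3. Can a break reach beyond one participant?** Only if three things hold: the letters are trial-wide, as {11a} and {16b} read; the result reaches someone who knows container letters; and other participants are still to be measured. Staff who count returned sachets ({11a}) or review supplement use at monthly visits ({11c}) might know letters. The section on oversight {5d} has the researcher assess reported events with the research team, and {17b} places no barrier between those people and the result.

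**Step 4. Bounds on exposure per break.** Inputs from the sample size section {14}: 72 randomised, 36 per group.

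- Others with the same letter: 36 − 1 = 35.
- Participants with the other letter: 36.
- Ceiling: 35 + 36 = 71, if the recipient knows every participant's letter.
- Floor: 0, if the result reaches nobody who knows a letter.

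The ceiling counts everyone randomised, including participants who may already have finished their 8 weeks and whose measurements can no longer be influenced. The number that matters is those still in follow-up, which the documents do not allow one to compute.

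**Step 5. How often might the trigger fire?** The documents give no event rate. For assumed per-participant rates p over 8 weeks, the chance of at least one mandatory break among 72 is 1 − (1 − p)^72:

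| Assumed p | Chance of at least one break |
|---|---|
| 0.5% | 30% |
| 1% | 52% |
| 2% | 77% |
| 5% | 97% |

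These are illustrations, not estimates. They count all breaks, needed and avoidable alike.

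**The case against.** The strongest case on the other side has four parts.

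1. *This is a condensed article.* Who authorises a break, who is told and how SAE is defined are commonly left to the full protocol. That holds for the silence on disclosure, which would not be a finding alone. It does not cover the trigger: {17b} states a positive rule, and following it produces the avoidable breaks.

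2. *SAE probably means serious.* The reference to regulatory reporting fits that reading, and the gastrointestinal example in {11b} stands in a list about stopping treatment, not unblinding. The interim analysis section {21b} also calls the intervention low risk. If serious was meant, fewer events trigger a break and the point shrinks. The text nevertheless says severe in both places, and even a serious event does not always require the code.

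3. *Spread to other participants is conjecture.* It needs a break, a leak beyond the designated person, a recipient who knows letters, and influence on a measurement. This stands. A reader might infer that a single break unblinds the trial, or that 71 allocations would be lost. The documents do not support that: they nowhere say that results of a break are circulated or that outcome assessors see letters, {17b} speaks of secure access, and {16b} and {16c} place assignment with someone outside the study.

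4. *A need test alone leaves the mechanism in place.* Correct: a clinically necessary break would reveal the letters in the same way. The remedy therefore also has to limit who learns the result.

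**Conclusion.** The point holds and is minor. The rule in {17b} makes code-breaking automatic for a class of event that, in the article's own usage, includes severe gastrointestinal symptoms, and it requires no clinical need. Since the sachets can be stopped blind, some breaks under this rule are avoidable. With what appear to be only two trial-wide letters, a break could also expose participants still in follow-up if its result reaches staff who know container letters.

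The size cannot be fixed from the documents. Neither the number of avoidable breaks nor any effect on an estimate can be derived, and 71 is a theoretical ceiling rather than an expectation. The conclusion rests on reading severe as written and on the letters being trial-wide; the second affects only the spread to others. No bias is demonstrated, and nothing in the sample size, power or significance level changes.

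**What to change.** Reword the section on unblinding {17b} so that:

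- an individual's code is broken only when the treating physician states that the allocation is needed for that participant's care;
- in all other cases the sachets are stopped, and the event is treated and reported blinded;
- SAE is written out as serious adverse event;
- the result of any break goes only to the treating physician and the oversight bodies, and not to outcome assessors, staff who handle or count sachets, or analysts.

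Emergency unblinding stays available, so participant safety is not reduced. The cost is protocol wording, with ethics committee approval under {25} if the change is classed as significant, and a documented reason for each break.

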## Data collection and management

### Plans for assessment and collection of outcomes {18a}

Our study will put in place a thorough plan for gathering and assessing data, including baseline and other trial results. We will collect data using validated questionnaires and reliable lab methods that were presented in previous sections of the protocol. To maintain data quality, we will provide training for assessors and use duplicate measurements where possible. All data collection forms will be stored in a separate online repository, distinct from the primary trial documentation. We will regularly review the data to ensure accuracy and completeness.

### Plans to promote participant retention and complete follow-up {18b}

Measures will include frequent follow-up phone calls or social media messaging, tracking of alternate contact information (first of kin), and compliance monitoring for the supplement.

### Data management {19}

The use of double data entry and rechecking outliers will promote data quality. Data will be securely stored in a password-protected database to which access will be limited to the authorized personnel.

### Confidentiality {27}

To protect participant confidentiality, we will anonymize data using unique ID codes during collection. We will share anonymized data only with authorized persons. Anonymized electronic records will be stored on a Google Sheet, and paper records will be kept in secure facilities. After the trial, we will destroy identifiable data after 5 years and securely archive anonymized datasets for future research, pending ethics approval.

### Plans for collection, laboratory evaluation and storage of biological specimens for genetic or molecular analysis in this trial/future use {33}

At the start and after eight weeks, we take blood samples. We store these samples at −80 °C in a central biobank at Mashhad University of Medical Sciences, labeling them with anonymous codes for possible future use. All specimens will be stored for possible further studies in the university laboratory.

## Statistical methods

### Statistical methods for primary and secondary outcomes {20a}

All statistical analyses will be conducted using SPSS software version 26. The primary outcome is the change in anthropometric measures and body composition parameters (body weight, BMI, waist circumference, hip circumference, waist-to-hip ratio, fat mass, fat-free mass, and visceral fat) from baseline to the end of the intervention. The secondary outcome includes (1) changes in systolic and diastolic blood pressure, (2) biochemical indices including fasting blood glucose, triglycerides, total cholesterol, HDL cholesterol, LDL cholesterol, TYG index, TC-to-HDL ratio, and FBS-to-HDL ratio, and (3) appetite parameters derived from the VAS questionnaire (satiety, hunger, fullness, prospective food consumption, and desire for specific foods). The primary outcome will be evaluated at a two-sided significance level of *p* < 0.05. To account for multiple secondary outcomes and reduce the risk of type I error inflation, the Benjamini–Hochberg false discovery rate (FDR) adjustment will be applied.

Baseline characteristics between the two study groups will be compared using independent t-tests (or Mann–Whitney *U* tests for non-normally distributed data) for continuous variables and chi-square tests for categorical variables. For within-group changes over time, paired t-tests (or Wilcoxon signed-rank tests) will be used. Between-group comparisons of changes in primary and secondary outcomes will be performed using repeated measures ANOVA or ANCOVA, adjusting for baseline values and potential confounders (e.g., age, sex, baseline BMI), provided model assumptions are satisfied. If assumptions are violated, appropriate non-parametric alternatives will be applied. Post-hoc tests with Bonferroni correction will be conducted when global tests indicate statistical significance.

The normality of continuous variables will be assessed using the Shapiro–Wilk test and by visual inspection of histograms and Q-Q plots. Homogeneity of variances will be checked using Levene’s test. These steps are essential to determine whether parametric or non-parametric statistical methods should be applied.

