### Objectives {7}

This study explores methods to prevent and manage obesity and its complications by examining a novel beverage powder supplement containing pasteurized *Akkermansia muciniphila*, green tea extract, and glucomannan konjac. Although the effects of each component have been previously investigated, the impact of combining these components has not been explored. The primary focus is on the supplement’s effects on body composition and anthropometric measurements, as well as metabolic parameters (including fasting blood glucose and serum lipid profile), blood pressure, and appetite, as secondary outcomes in overweight or obese adults. We hypothesize that this supplement, when combined with lifestyle interventions such as dietary therapy and physical activity, is more effective than lifestyle interventions alone in improving these outcome variables.

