#### Sample size {14}

The sample size was calculated using the formula for the difference between two independent means, considering the mean and standard deviation of fat mass changes observed in the intervention (24.3 ± 1.8) and control (26.7 ± 2.8) groups as reported by D Roberts et al. [24]. With a type I error rate set at *α* = 0.05 and a statistical power of 1 − β = 0.90 aimed at detecting a standardized effect size of at least Δ = 0.80, the minimum required sample size for each group was determined to be 27 participants. However, after accounting for a potential dropout rate of 20%, this figure increased to 36 participants per group. Ultimately, a total of 72 overweight or obese adults will be recruited.

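### Eight measures form the primary outcome at two-sided 0.05 with no success rule and no multiplicity control, so a claim resting on any one of them does not carry a 5% error rate

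*Protocol article*

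**What the plan says.** The statistical methods section {20a} treats as one primary outcome the baseline-to-end change in eight variables. The definition begins "The primary outcome is the change in anthropometric measures and body composition parameters (body weight, BMI, waist circumference, hip circumference", and the full list is "body weight, BMI, waist circumference, hip circumference, waist-to-hip ratio, fat mass, fat-free mass, and visceral fat". It then sets the level: "The primary outcome will be evaluated at a two-sided significance level of *p* < 0.05". The next sentence introduces multiplicity control with an explicit scope: "To account for multiple secondary outcomes and reduce the risk of type I error inflation, the Benjamini–Hochberg false discovery rate (FDR) adjustment will be applied". Later in the same section, a second correction is mentioned: "Post-hoc tests with Bonferroni correction will be conducted when global tests indicate statistical significance".

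Other sections do not narrow the list. The objectives {7} name two domains and no variable: "The primary focus is on the supplement’s effects on body composition and anthropometric measurements". The outcomes section {12} describes all the anthropometric and body-composition measurements under a plural primary heading, with no lead variable. The sample size section {14} works from one variable only, "fat mass changes observed in the intervention (24.3 ± 1.8) and control (26.7 ± 2.8) groups", but does not call fat mass the primary outcome. The protocol describes no composite score, testing order, division of alpha or requirement that all measures be significant.

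**The concern.** The authors saw that many tests inflate type I error and provided for it, but only in the secondary family. The primary family has eight members and one undivided 0.05. A reader of the final report could not tell from this protocol what result meets the primary objective.

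The two natural rules each break a stated property of the design. If a significant result on any one measure counts, the 5% level does not apply to the claim being made. If all eight must be significant, the 90% power, calculated for one variable, does not apply. With the rule left open, the choice could be made after the results are known.

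**Working it through.** **Inputs.** Eight primary measures, two-sided 0.05 and no adjustment within the primary family (section {20a}); alpha 0.05, power 0.90, standardized difference 0.80, 27 per group before dropout and 36 after (section {14}). The correlations between the change scores are not given. They are assumed below and varied.

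**The plan's own figure.** The usual formula is n = 2(z_α + z_β)²/d².
- One-sided 0.05: 2(1.645 + 1.282)²/0.64 = 26.8, so 27 per group, which matches.
- Two-sided 0.05: 2(1.960 + 1.282)²/0.64 = 32.8, so 33 per group, which does not match.

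The stated 27 is therefore recovered only with a one-sided level. That is a separate sample-size matter, but it affects how the power figures below should be read.

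**If any one of eight suffices.** Under independence the familywise error is 1 − 0.95⁸ = 0.337. Independence cannot hold here. BMI change is close to weight change rescaled by height, waist-to-hip ratio is computed from waist and hip, and weight is close to fat plus fat-free mass. Counting weight and BMI as one test already lowers the independence value to 1 − 0.95⁷ = 0.302.

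Simulating eight two-sided z-tests at 0.05 with a common correlation (400,000 runs each) gives:

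| Assumed correlation | At least one false positive, either direction | One direction only |
|---|---|---|
| 0.3 | 30% | 15% |
| 0.5 | 25% | 13% |
| 0.7 | 19% | 10% |
| 0.9 | 12% | 6% |
| 1.0 | 5% | 2.5% |

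A structured simulation built weight as fat plus fat-free mass, BMI from weight and height, and waist-to-hip ratio from waist and hip (27 per group, 20,000 runs per setting). Assumed correlations were 0.3 to 0.85 for waist and hip with weight, and 0.4 to 0.8 for visceral fat with fat mass. The either-direction familywise error ran from 24.7% down to 20.1%.

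**If all eight must be significant.** Take a true difference of 0.80 on every measure and 36 per group with no loss. Power for one measure is 0.924 (normal approximation). For all eight it is 0.924⁸ = 0.53 if independent, and by simulation about 0.77 at correlation 0.7 and 0.85 at 0.9. With 27 per group the independent value is 0.836⁸ = 0.24.

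**Cost of repairing by Bonferroni instead.** Each test would use 0.05/8 = 0.00625. Holding 90% power at d = 0.80 needs 51 per group, or 64 after 20% dropout (51/0.8 = 63.75). With 36 per group, power per measure is about 72% (t-test) to 75% (normal approximation). With 27 per group it is 54% to 58%.

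**The case against.** Four points can be made for the plan.

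- **The protocol speaks of one primary outcome, in the singular.** It does, and it never states that success on any one measure is enough. A reader might infer that the trial will declare success on whichever measure crosses 0.05; the text does not say so. The defect is an undefined success rule, and the inflation follows under one reading of it. The singular does not cure this, because no composite or joint test is described.
- **Bonferroni is mentioned.** It is tied to post-hoc tests after a significant global test and is not stated to apply across the eight measures.
- **The measures are strongly related, so the inflation may be modest.** This stands in part. A reader might take 20–34% as the established error rate. The documents do not support that: they give no correlations, 34% needs eight independent tests that cannot occur here, and 20% is not a floor, since common correlations of 0.8 to 0.9 give 16% to 12%. This is also a superiority trial, so an error that supports a benefit claim is about half as frequent, although the favourable direction is less clear for fat-free mass.
- **A statistical analysis plan could settle it.** It could add detail, but the protocol already fixes the primary family, its level and the scope of the adjustment. Naming one primary outcome later would change the protocol.

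One further caution concerns power. It would be wrong to blame the whole fall from 90% to between 54% and 58% at 27 per group under Bonferroni on multiplicity. Two-sided power for fat mass alone at d = 0.80 is only about 82% with 27 per group, because of the sample-size calculation itself.

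**Conclusion.** The point holds. As written, the plan does not control error at 5% for a primary claim that rests on any one of the eight measures, and it does not say what claim it intends. Under the any-one reading the excess over 5% is certain at any correlation below 1. Its size depends on assumed correlations: about 20–25% in the structured simulations and roughly 12–30% across common correlations of 0.9 to 0.3, with about half the common-correlation figures if only one direction is counted. Under the all-eight reading the stated 90% power is not reached at any of the correlations tried, up to 0.9, even with all 36 per group retained. This should be corrected before unblinding because it determines what the trial's main result means.

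**What to change.** In section {20a}, and to match in the objectives, outcomes and registry entry, name change in fat mass from baseline to week 8 as the single primary outcome, tested at two-sided 0.05. It is the variable the trial was sized on, so this choice needs no split of alpha and no extra participants on account of multiplicity. Move the other seven measures into the secondary family that already receives the Benjamini–Hochberg adjustment. Make the change by dated amendment before the data are unblinded, with ethics approval and registry documentation as section {25} requires. Recruitment was expected to finish on October 23, 2025, so timing matters.

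The cost is more than wording. Seven measures lose unadjusted primary status, and the larger secondary family can change the adjusted results of the existing secondary outcomes. A prespecified testing order or an adjusted primary family would also cure the defect, but Bonferroni over eight costs the power shown above. Dropping weight or BMI as a separate test is optional.
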